# Combination of Electroacupuncture and Medication for Patients With Tinnitus Associated With Idiopathic Sudden Sensorineural Hearing Loss: Protocol for a Prospective Randomized Controlled Trial

**DOI:** 10.2196/69163

**Published:** 2025-05-14

**Keywords:** idiopathic sudden sensorineural hearing loss, tinnitus, acupuncture, study protocol, electroacupuncture, adjunctive therapy

## Abstract

**Background:**

Tinnitus, a common and troublesome symptom of idiopathic sudden sensorineural hearing loss (ISSNHL), is the perception of sound without any external or internal sound source. The etiology of ISSNHL accompanied by tinnitus remains unclear. Tinnitus often occurs alongside or before hearing loss and can severely impact patients’ quality of life, leading to psychological stress and emotional distress. Current treatments primarily focus on improving hearing loss while neglecting tinnitus treatment. Electroacupuncture (EA), a technique widely applied in China for tinnitus management, may become a promising intervention by addressing both auditory and psychological symptoms.

**Objective:**

This study aims to conduct a double-center, assessor-blinded, prospective randomized pilot clinical trial to explore the potential effects and feasibility of EA combined with medication for patients with ISSNHL accompanied by tinnitus, and to generate preliminary data to inform future large-scale trials of EA as an adjunctive therapy for this condition.

**Methods:**

In this double-center, assessor-blinded, randomized controlled trial, 60 patients with ISSNHL accompanied by tinnitus will be randomly allocated to either the EA group, receiving EA combined with medication, or the control group, receiving standard medication treatment, for a total treatment duration of 4 weeks. Follow-up assessments will be conducted at weeks 2 and 4, and at 1, 2, and 3 months after treatment. The feasibility primary outcomes are recruitment rate, adherence rate, data completeness, and safety outcomes. The primary outcome measures will include pure tone audiometry, tinnitus matching, and the Tinnitus Handicap Inventory, while the secondary outcome measures will comprise speech-recognition thresholds in noise, the Self-Rating Anxiety Scale, and the 36-item Short Form Health Survey Questionnaire.

**Results:**

This study began recruitment on July 15, 2024, and is scheduled to conclude on August 31, 2025. To date, 42 participants have been enrolled, with 35 having completed the intervention and posttreatment assessments (control group: n=21; EA group: n=14). Following protocol publication, data compilation and analysis will be conducted, with results anticipated to be published in a relevant journal in 2026.

**Conclusions:**

This pilot trial is expected to provide critical insights into the feasibility of integrating EA with standard medication for managing ISSNHL with tinnitus. By generating preliminary evidence on its practicality and potential benefits, this study aims to inform the design and sample size estimation of future multicenter trials, potentially advancing nonpharmacological treatment options for this challenging condition.

**Trial Registration:**

Chinese Clinical Trial Registry ChiCTR2400086802; https://tinyurl.com/mtxthpzj

**International Registered Report Identifier (IRRID):**

DERR1-10.2196/69163

## Introduction

Idiopathic sudden sensorineural hearing loss (ISSNHL) is characterized by a rapid, unexplained sensorineural hearing loss of at least 30 dB over 3 contiguous frequencies within 72 hours, typically occurring unilaterally [1]. The incidence of ISSNHL is estimated to range from 5 to 20 cases per 100,000 individuals annually. However, some studies suggest that this figure may be underestimated, as those who recover swiftly often do not seek medical care [2]. The tinnitus associated with ISSNHL lacks a precise definition. Clinically, it is typically described as tinnitus that arises simultaneously with, or within hours to days after, the onset of ISSNHL. In some cases, tinnitus may even precede the hearing loss by a few hours to several days. However, patients often pay more attention to symptoms such as tinnitus, aural fullness, or dizziness, which may lead them to overlook the initial onset of ISSNHL. Previous clinical studies have reported a tinnitus incidence ranging from 69.8% to 93.3%. A multicenter study in China found that, among 1024 patients with ISSNHL, 90.1% experienced tinnitus—a prevalence notably higher than that of vestibular symptoms, aural fullness, or dizziness [3,4]. Patients with tinnitus frequently endure considerable psychological stress, mood disturbances, and sleep disorders, all of which can impair their performance at work or in their studies. In more severe cases, these individuals may also develop anxiety and depression [2,5]. The alleviation of tinnitus symptoms typically progresses more slowly than the recovery of hearing. Even after hearing is restored, some patients may continue to experience persistent tinnitus, which can significantly diminish their quality of life. Consequently, clinicians should prioritize addressing tinnitus in tandem with treating hearing loss [6,7].

The pathogenesis of ISSNHL with tinnitus remains unclear [8]. It is generally believed that the onset and progression of tinnitus are related not only to peripheral hearing impairment but also to abnormal brain activity [9], including disrupted intra- and internetwork connectivity, psychological factors, and stress hormones [10,11]. Currently, treatment for ISSNHL accompanied by tinnitus primarily aims to address the underlying hearing loss [6,12]. Restoring auditory function can help disrupt the mechanisms that induce tinnitus, reestablish central auditory input, and prevent its progression [13,14]. The standard treatment approach involves corticosteroid administration, either systemically or through intratympanic injection [1]. The American clinical practice guideline for ISSNHL [1] does not provide specific recommendations for the treatment of comorbid tinnitus, but it highlights its prevalence, refractoriness, and the potential economic and psychological burdens associated with the condition.

The Chinese guideline for the diagnosis and treatment of sudden hearing loss [15] classifies ISSNHL into 4 types based on audiometric patterns: low-frequency descending, high-frequency descending, flat, and total. Different audiometric patterns may suggest distinct pathogenic mechanisms for ISSNHL. For example, the low-frequency descending type is associated with endolymphatic hydrops, the high-frequency descending type with hair cell damage, and the flat type may reflect a broader inner ear injury mechanism, such as stria vascularis dysfunction or inner ear vascular spasm [16]. These differences may influence treatment responses and prognosis [17].

Acupuncture, a therapy that involves the insertion of fine needles into the body followed by manipulation techniques such as lifting, thrusting, and twisting, was described as a treatment for tinnitus as early as the 5th century BCE in China [18]. Although the clinical practice guideline developed by Tunkel et al [19] does not mention acupuncture for the treatment of persistent tinnitus due to the lack of high-quality randomized controlled trials (RCTs), the expert panel acknowledged that many patients with persistent or bothersome tinnitus seek acupuncture therapy. Additionally, a European epidemiological study showed that the average annual out-of-pocket expenditure for European patients with tinnitus was €565 (US $640), with €183 (US $207) spent on acupuncture, homeopathy, and osteopathy. These patients were willing to pay 1.6-7 times their monthly income for complete tinnitus relief [20]. Furthermore, emerging evidence suggests that acupuncture, including electroacupuncture (EA), may modulate functional connectivity within brain networks, such as those involving the insula and frontal regions, potentially contributing to its therapeutic effects on tinnitus and possibly extending to cases associated with ISSNHL [21-24]. EA is a safe and effective intervention that is easier to standardize and more controllable than manual acupuncture, providing prolonged stimulation, precise intensity control, and enhanced acupuncture sensation [25,26].

This study aims to investigate the feasibility and potential effects of EA combined with medication on hearing and tinnitus outcomes in patients with ISSNHL and tinnitus, generating preliminary data to support future research on EA as an adjunctive treatment for ISSNHL.

## Methods

### Design and Setting

The study is designed as a prospective, single-blinded RCT. It will take place in the clinics of Beijing Tongren Hospital, Capital Medical University, and the Acupuncture and Moxibustion Hospital, China Academy of Chinese Medical Sciences (CACMS). Eligible participants will be randomized in a 1:1 ratio to either the EA group (EA plus medication) or the control group (standard medication alone). This pilot trial will apply a longitudinal follow-up design, with a baseline assessment before enrollment (t–1), allocation and intervention initiation at t0, on-treatment follow-ups at week 2 (t1), week 4 (t2), and posttreatment follow-ups at 1 month (t3), 2 months (t4), and 3 months (t5) after intervention completion, barring loss to follow-up. This trial will be reported in accordance with the CONSORT (Consolidated Standards of Reporting Trials)-EHEALTH (see Multimedia Appendix 1) statement, which defines standard reporting items for RCTs [27]. Participant recruitment began on July 15, 2024, with the study scheduled to continue until December 2025. The flowchart is illustrated in Figure 1, and the overall procedure is presented in Table 1.

**Figure 1 figure1:**
[figure not shown]
The enrollment process of the trial. EA: electroacupuncture.

**Table 1 table1:** Overall procedure of this study.

Stages					Enrollment		Allocation		On-treatment follow-up				Posttreatment follow-up						
Time point					–t_1_		t_0_		t_1_		t_2_		t_3_		t_4_		t_5_		
**Enrollment**																			
	Eligibility screening			✓		N/A^a^		N/A		N/A		N/A		N/A		N/A			
	Informed consent			✓		N/A		N/A		N/A		N/A		N/A		N/A			
	Allocation			N/A		✓		N/A		N/A		N/A		N/A		N/A			
**Interventions**																			
	Control group			N/A		N/A		✓		✓		N/A		N/A		N/A			
	Electroacupuncture group			N/A		N/A		✓		✓		N/A		N/A		N/A			
**Assessments**																			
	**Feasibility outcomes**																		
		Recruitment rate		N/A		N/A		N/A		N/A		✓		N/A		N/A			
		Adherence rate		N/A		N/A		N/A		N/A		✓		N/A		N/A			
		Data completeness		N/A		N/A		N/A		N/A		✓		N/A		N/A			
		Adverse events		N/A		N/A		✓		✓		✓		✓		✓			
	**Exploratory outcomes**																		
			Pure tone audiometry	N/A		✓		✓		✓		✓		✓		✓			
			Tinnitus matching	N/A		✓		✓		✓		✓		✓		✓			
			Tinnitus Handicap Inventory	N/A		✓		✓		✓		✓		✓		✓			
	**Secondary outcomes**																		
			Speech-recognition thresholds in noise	N/A		✓		✓		✓		✓		✓		✓			
			Self-Rating Anxiety Scale	N/A		✓		✓		✓		✓		✓		✓			
			36-item Short Form Health Survey Questionnaire	N/A		✓		✓		✓		✓		✓		✓			

^a^N/A: not applicable.

### Eligibility Criteria

Inclusion criteria included the following: a diagnosis of ISSNHL [15], defined as sudden hearing loss (≥30 dB) within 72 hours affecting 3 consecutive frequencies, and accompanied by tinnitus; between 18 and 65 years of age at the time of recruitment; pure tone audiometry (PTA) results showing a flat drop audiogram; onset of hearing loss within 1 week before randomization; clear consciousness, normal cognition, and unaffected basic communication.

Exclusion criteria were hearing loss from other causes (eg, congenital deafness, conductive deafness, presbycusis, large vestibular aqueduct syndrome, Meniere disease, tumors, or deafness due to systemic genetic diseases); having received medication or acupuncture treatment within the past 6 months, or having an allergy to the treatment medication; pregnancy or lactation in females; presence of severe systemic diseases or psychiatric disorders; and participation in other trials.

### Ethical Considerations

Ethics approval was obtained from the Ethics Committee of Beijing Tongren Hospital, Capital Medical University (approval number TREC2024-KY060). Before the trial begins, researchers must provide participants with detailed information about the clinical trial, including its purpose, procedures, potential benefits and risks, alternative treatment options, and the rights and responsibilities of the participants. Participants will also be informed that they are free to withdraw consent at any time during the study. They must fully understand this information and provide their consent by signing an “informed consent form” before the clinical trial can commence.

### Enrollment, Randomization, and Blinding

Recruitment will be conducted through WeChat (Tencent Holdings Limited) public account notifications, roll-up banners at clinic entrances, and collaboration with community committees for promotion.

Stratified block randomization will be performed according to the study center. Both groups will be assigned in a 1:1 ratio to the EA and control groups using a block size of 4. [name], a statistician from the Evidence-Based Medicine Center at CACMS, will serve as the randomization coordinator and will be responsible for generating the stratified block randomization sequence using SAS 9.3 software (SAS Institute). She will not participate in the trial’s implementation or data analysis. After obtaining informed consent and before initiating treatment, the treating physician at each center will contact the randomization coordinator by phone to receive the randomization number and group assignment.

Because of the nature of acupuncture, it is not possible to blind the acupuncturists or participants. However, steps will be taken to minimize bias from single blinding as much as possible. Acupuncturists will receive specialized training before participating in the study and will be instructed not to discuss treatment procedures or outcomes. They will also be excluded from evaluating the results. Patients will be treated separately to prevent contact between participants. The randomization staff and acupuncturists will have access to the assignment information, but the outcome evaluators and statisticians will remain blinded throughout the entire clinical trial. Statisticians will speculate on the group allocation before data analysis to assess the efficacy of blinding, and unblinding will only occur after the completion of data analysis.

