## Results

This study began recruitment on July 15, 2024, and is scheduled to conclude on August 31, 2025. To date, 42 participants have been enrolled, with 35 having completed the intervention and posttreatment assessments (control group: n=21; EA group: n=14). Following protocol publication, data compilation and analysis will be conducted, with results anticipated to be published in a relevant journal in 2026.

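### A single block size of 4 per centre, published before recruitment was due to end in an open-label trial, would let anyone who sees a centre's full sequence predict up to a third of assignments with certainty

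*Protocol article*

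**What the plan says.** The section Enrollment, Randomization, and Blinding of the protocol article sets out the allocation method.

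- Stratification: "Stratified block randomization will be performed according to the study center". The Objective describes two centres: "double-center, assessor-blinded, prospective randomized pilot clinical trial".
- Ratio and block: "Both groups will be assigned in a 1:1 ratio to the EA and control groups", "using a block size of 4". No varying or withheld sizes are mentioned.
- Release of assignments: after consent and before treatment, "the treating physician at each center will contact the randomization coordinator by phone to receive the randomization number and group assignment". The list is made and held by a statistician who takes no part in trial conduct or analysis.
- Masking: "it is not possible to blind the acupuncturists or participants". Outcome evaluators and statisticians are masked.

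The article is dated 14 May 2025. Its Results section says "This study began recruitment on July 15, 2024, and is scheduled to conclude on August 31, 2025", and Design and Setting has the study running to December 2025. On progress, Results says "To date, 42 participants have been enrolled". The Sample Size section sets the target at 60, 30 per group.

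**The concern.** Holding the list centrally and releasing assignments only after consent keeps the list itself hidden. It does not stop someone from counting. Treatment is visible, so past assignments at a centre can be known. If every block holds exactly two of each arm, the fourth assignment is always determined, and so is the third whenever the first two agree. Masked assessors protect measurement, not who enters the trial and when.

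If the next assignment is foreseeable, prognosis could influence who is invited or when the call is made. The Discussion treats days from onset to treatment as an independent predictor of outcome, and eligibility allows up to one week, so patients differ on it and the physician can see it before phoning. The Statistical Analysis section adjusts only for baseline hearing-loss severity, and only if the groups differ significantly on it. An imbalance in days since onset would not be adjusted. The Sample Size section says the results will supply effect sizes for later trials, so a distortion here would carry into their planning.

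**Working it through.** The article gives no figure for predictability, so there is none to reproduce.

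**Inputs from the article:** block of 4, 1:1 (two EA and two control per block), two centres, target 60, 42 enrolled at writing, so 60 − 42 = 18 remaining.

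**Assumption:** the observer sees every earlier assignment at the centre, knows the block size, and guesses the arm with more places left in the block (a coin toss when equal).

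**Enumeration of the 6 equally likely blocks of 4:**

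| Position in block | Chance the assignment is certain | Chance of a correct guess |
|---|---|---|
| 1 | 0 | 1/2 |
| 2 | 0 | 2/3 |
| 3 | 1/3 | 2/3 |
| 4 | 1 | 1 |
| Average | (4/3)/4 = 33.3% | (17/6)/4 = 17/24 = 70.8% |

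In whole blocks this is 60 × 1/3 = 20 certain assignments over the trial, or 18 × 1/3 = 6 of the 18 remaining.

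**Incomplete last blocks.** The number per centre is not given, so two cases bracket it.
- 30 per centre (60 split evenly) is 7 blocks plus 2 patients. Certain: 7 × 4/3 = 9.33 of 30 = 31.1%. Correct guesses: 7 × 17/6 + 1/2 + 2/3 = 21.0 of 30 = 70.0%.
- 9 per centre (18 split evenly, on a fresh list) is 2 blocks plus 1 patient. Certain: 2 × 4/3 = 2.67 of 9 = 29.6%, or about 5 of 18. Correct guesses: 2 × 17/6 + 1/2 = 6.17 of 9 = 68.5%.

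**Effect of varying sizes.** Each block size is drawn with equal probability. The observer knows the set of sizes but not their order, and updates after each assignment. Values are exact for 9 per centre; for 30 per centre the varying-size rows are simulated.

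| Block sizes | Certain, 9 per centre | Certain, 30 per centre | Correct guess, 9 per centre | Correct guess, 30 per centre |
|---|---|---|---|---|
| 4 only | 29.6% | 31.1% | 68.5% | 70.0% |
| 2, 4, 6 | 3.0% | 3.8% | 67.5% | 69.9% |
| 4, 6 | 5.8% | 5.7% | 66.2% | 68.8% |
| 4, 6, 8 | 2.6% | 2.4% | 65.2% | 67.4% |

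Varying the sizes nearly removes certainty but changes overall guessability little. Including blocks of 2 brings back most of the guessability that larger blocks take away.

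**The case against.** A fixed block of 4 is a common choice and contradicts nothing else in the article. The list is made by an independent statistician and each assignment is released only after consent, which prevents reading ahead and makes rejection after assignment harder. The one-week onset limit leaves little room to hold a patient back for a preferred slot. The trial is a pilot: its feasibility outcomes are descriptive, and its efficacy outcomes are exploratory. At least 42 of the 60 assignments were made before the article appeared, so a change can reach at most 18/60 = 30% of the trial.

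All of this stands and limits the weight of the point. It does not remove it, because selective invitation remains possible and none of the listed safeguards addresses counting within a block.

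Three stronger readings are tempting, and the article does not support them.

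- A reader might infer that the physician who phones also recruits and sees every assignment. The text says only that the treating physician at each centre makes the call. Recruitment is described as notices, banners and community promotion. If several physicians share a centre without sharing assignments, predictability is lower.
- A reader might take 33% and 71% as what happened. They are what a fully informed observer could achieve.
- A reader might take the completers (21 control, 14 EA) as a sign of steering. Blocks of 4 in two centres allow an imbalance of at most 2 per centre, so 42 enrolled gives arms between 19 and 23. The 42 − 35 = 7 patients not yet complete can account for the gap: 21 enrolled in each arm with all 7 in the EA arm gives exactly 21 and 14.

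**Conclusion.** The point holds as a modest, avoidable risk of selection bias. For someone who sees a centre's whole sequence and knows the block size, up to one third of assignments are certain and up to about 71% can be guessed. The article does not establish that such a person exists at either centre or decides on enrolment, and offers no evidence that patient selection was affected. The 18 remaining patients are an undated count, so fewer may have been unassigned when the block size was published. What is at stake is mainly the effect-size estimate meant for later trials; no confirmatory claim rests on it. It is worth considering because the remedy is nearly free.

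**What to change.** For patients not yet randomized, the coordinator should issue a new list per centre with randomly varying block sizes that avoid size 2, for example 4, 6 and 8. The sizes should be withheld from the sites and from publications until recruitment ends. The trial report should state how many patients were randomized under each list. For patients already randomized, that disclosure is all that can be done.

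The gain is in certainty, and the change should not be presented as making assignments unpredictable overall.

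The cost is a short SAS run and a dated protocol note. The price is balance: within a block of 8 the arms at a centre can differ by up to 4, against 2 now. If the old list is abandoned in mid-block, its leftover difference of up to 2 can add to that, so the note should record where each centre's old list stopped. If recruitment is already complete, only the reporting step remains.

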### Sample Size

As previous RCTs have not investigated EA as a combination intervention in patients with ISSNHL with tinnitus, it is challenging to determine the optimal sample size through power calculation. Therefore, rather than performing a formal sample size estimation, this trial will adopt a preliminary exploratory clinical pilot design to estimate the appropriate sample size [28]. However, to preliminarily assess the feasibility of the proposed intervention, we will ensure an adequate number of participants in our experimental design by adhering to the established guideline of a minimum of 12 participants per group for pilot studies [29]. A previous study suggested that each group should have a sample size ranging from 20 to 25 cases for exploratory clinical trials assessing the effectiveness of intervention measures [30]. Therefore, in this study, each group will consist of 25 patients, resulting in a total of 50 cases across the 2 groups. To account for a potential dropout rate of 20%, we will recruit a total of 60 patients (30 per group). The results of this study will provide effect size data for calculating sample sizes in future large-scale RCTs.

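### Recruiting 60 patients does not leave the planned 25 per group after 20% dropout: it leaves 24 per group (48 in total), a minor arithmetic slip

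*Protocol article*

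**What the plan says.** The Sample Size section of the protocol article makes no power calculation: "rather than performing a formal sample size estimation, this trial will adopt a preliminary exploratory clinical pilot design". It relies on two published rules of thumb. One is a floor, "a minimum of 12 participants per group for pilot studies". The other is a range: "each group should have a sample size ranging from 20 to 25 cases for exploratory clinical trials". It takes the upper end of that range and states that "each group will consist of 25 patients, resulting in a total of 50 cases across the 2 groups".

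It then raises the number to allow for losses: "To account for a potential dropout rate of 20%, we will recruit a total of 60 patients (30 per group". The Abstract gives the same total of 60, and Design and Setting confirms equal allocation ("Eligible participants will be randomized in a 1:1 ratio to either the EA group"). The inflation formula is not shown, and no other section revises these numbers.

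**The concern.** The section gives three numbers that must agree: the size wanted after losses (25 per group), the loss rate (20%) and the number recruited (30 per group). Any two of them fix the third. Here they conflict, because 20% of 30 is 6 and removing 6 leaves 24.

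At stake is the accuracy of the stated dropout allowance. A reader would take it that the trial can lose one patient in five and still have 25 per group, when it can lose only one in six. Because the pilot is meant to inform later trials, the same inflation step could be copied into a larger study, where the absolute shortfall would be bigger.

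**Working it through.** **Inputs, all from the Sample Size section except the ratio**

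- Size wanted after dropout: 25 per group, 50 in total
- Dropout rate: d = 0.20
- Recruited: 30 per group, 60 in total
- Allocation: 1:1 (Design and Setting)

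**1. Reproducing the plan's figure.** Multiplying by (1 + d) gives 25 × 1.2 = 30 per group and 50 × 1.2 = 60 in total. Both match the protocol exactly.

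**2. What 60 recruited patients leave.** Retained = recruited × (1 − d): 30 × 0.8 = 24 per group and 60 × 0.8 = 48 in total. The shortfall is 25 − 24 = 1 per group, or 50 − 48 = 2 overall.

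**3. What 25 per group would need.** Recruited = wanted / (1 − d): 25 / 0.8 = 31.25, rounded up to 32 per group, which is 64 in total. As a check, 32 × 0.8 = 25.6, whereas 31 × 0.8 = 24.8 falls short. Inflating only the total gives 50 / 0.8 = 62.5, so 63, and equal groups bring that to 64.

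**4. The dropout rate that 60 really covers.** 1 − 50/60 = 0.167, or 16.7%.

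**5. Size of the effect.** For a comparison of two equal groups with the same standard deviation, the standard error scales with 1/√n. The ratio at 24 against 25 per group is √(25/24) = 1.021, about 2% wider.

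Suppose, as an assumption, that each patient drops out independently with probability 0.20. A group of 30 then keeps at least 25 with probability 0.43, at least 24 with probability 0.61, and at least 20 (the bottom of the cited range) with probability 0.97.

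| Recruited per group | Dropout | Left per group | Left in total |
|---|---|---|---|
| 30 | 20% | 24 | 48 |
| 30 | 16.7% | 25 | 50 |
| 32 | 20% | 25.6 | 51.2 |

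**The case against.** The best defence is that nothing depends on the 25. It was not derived from power or precision but is the top of a cited range, and 24 lies within that range and at twice the cited minimum of 12. The 20% is described only as a possible rate, and any rate up to 16.7% keeps 25. The Statistical Analysis section also says that efficacy analyses include everyone randomized, so the planned analysis set is 60. All of this stands as a limit on the importance of the point.

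It does not remove the inconsistency. The section itself inflates for dropout, so its 25 can only mean the number left afterwards. Analysing everyone randomized does not make the numbers agree either. The article does not say how missing values enter the analysis, so the number of completers may still matter in practice.

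Two stronger readings are tempting. First, a reader might treat the multiplication by 1.2 as established. It is the obvious route to exactly 30 and 60, but the article shows no formula, so it remains an inference. Second, the section goes on to say "The results of this study will provide effect size data for calculating sample sizes in future large-scale RCTs", and a reader might infer that the shortfall makes the pilot unfit for that purpose or will lead to a badly sized main trial. The documents do not support this. Precision is almost the same at 24 and 25 per group, so correcting the dropout figure would change little in that respect. The article does not say that the pilot's point estimate will be the main trial's target difference, and it gives no effect size from which the consequence could be calculated.

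**Conclusion.** The statement is wrong as written, and the matter is minor. With 60 recruited and 20% dropout, the expected number remaining is 24 per group (48), not 25 (50). The true allowance for keeping 25 is 16.7%.

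This rests only on the section's own three numbers, on equal groups, and on dropout meaning a fraction of those recruited, which is the usual sense. The contradiction holds whichever formula the authors used. It does not threaten the pilot's feasibility aims, alters no stated power or significance level, and gives no reason to recruit more patients.

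**What to change.** Keep the target of 60 and replace the dropout sentence with wording such as:

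> *Sixty patients (30 per group) will be recruited. With 20% dropout, 24 per group (48 in total) are expected, which is within the cited range of 20 to 25; 25 per group is reached if dropout is at most 16.7%.*

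This changes one sentence. Its only downside is a slightly less favourable stated figure. Recruitment, procedures and analyses are unaffected. The recruitment rate, a primary feasibility outcome defined against the target sample size, also keeps its denominator of 60.

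The alternative is to raise the target to 64 (32 per group) so that 25 remain at 20% dropout. That would be consistent too, but it would change that denominator during recruitment (the Results section reports 42 already enrolled) to gain about one patient per group. The restatement is the better choice.
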